# A 12 week, randomized, double-blind, placebo-controlled clinical trial for the evaluation of the efficacy and safety of HT083 on mild osteoarthritis

**DOI:** 10.1097/MD.0000000000020907

**Published:** 2020-07-10

**Keywords:** *Commiphora myrrha*, clinical trial, HT083, osteoarthritis, *Paeonia lactiflora*, pain

## Abstract

**Background::**

The increasing prevalence of osteoarthritis among the old population worldwide is a great concern. Two of the biggest complaints of OA patients are joint pain and inflammation. Currently, people are relying on non-steroidal anti-inflammatory drugs (NSAIDs) and steroids to control pain and inflammation. However, long-term use of these pharmaceutical drugs has negative health consequences in the elderly, including gastro-intestinal, respiratory, and renal diseases. Natural products are receiving more attention than ever as alternative treatments against OA for their efficacies and safety. The root of *Paeonia lactiflora* Pal and the gum resin of *Commiphora myrrha* have been used as analgesics and anti-inflammatory agents since ancient time. A new herbal formula composed of *P. lactiflora* root and *C. myrrha* gum resin extracts, known as HT083, has shown promising antinociceptive and anti-inflammatory effects in a rodent model of OA. We design this study to investigate the safety and the efficacy of HT083 to prevent OA in patients with mild OA.

**Methods::**

This is a randomized, double-blind, and placebo-controlled study. A total of 100 eligible participants will be divided into two groups and will be given HT083 and a placebo for 12 weeks in 1:1 ratio. Treatment results will be assessed using a visual analog scale (VAS), Korean-Short Form health survey-36 score (SF-36), personal evaluation, and laboratory analysis.

**Discussion::**

This trial is expected to provide clinical evidence on the effectiveness and the safety of HT083 as a natural treatment for mild OA.

**Trial registration::**

Korean Clinical Research Information Service (CRIS) number KCT0004925 Registered on 2020.04.16.

## Introduction

1

Osteoarthritis (OA) is known as a degenerative joint disease that affects millions of elderly people throughout the world. In most cases, OA patients experience synovial inflammation and cartilage loss, which causes pain and immobility.^[1]^ Nearly 50% of the people aged 65 or older on a global scale are believed to have OA symptoms.^[2]^ The pharmacological drugs such as non-steroidal anti-inflammatory drugs (NSAIDs) and steroids that are currently being used to manage OA pain and inflammation have adverse health effects if used for a long time. As a consequence, natural medicines, for their efficacy and safety, are being prioritized as a treatment for OA.

*Paeonia lactiflora* Pall root and *Commiphora myrrha* (Nees) Engl. gum resin are known for their pain-relieving and anti-inflammatory properties.^[3,4]^ The application of these herbs as traditional medicines dates back to ancient time. The use of herbal formula in Chinese medicine has been practiced for centuries for better functionality and safety than the individual herbs.^[5]^ An herbal formula composed of *P. lactiflora* and *C. myrrha* extracts named as HT083 has shown potent antinociceptive, anti-inflammatory, and cartilage protective activities in an animal model of OA in our previous study. We hypothesize that HT083 will prevent OA pain and inflammation in human. This placebo-controlled double-blind study will evaluate the efficacy and safety of HT083 in human subjects with mild OA.

## Methods and analysis

2

### Study design

2.1

This is a randomized, 12-week, double-blind, placebo-controlled study. The current protocol is registered at Neonutra Co. Ltd. (protocol number NM_HT083hn, version 1.1) on 14 Oct 2019 sponsored by Neumed Co., Ltd. The participants will be recruited at Uijeongbu St. Mary's Hospital, The Catholic University of Korea. After obtaining a written consent from all the participants, the qualified subjects will be randomly divided into HT083 and placebo groups. The treatment will continue for 12 weeks, and during that period, the participants will be provided necessary guidance on maintaining daily diets and activities. The subjects will be required to visit the hospital four times throughout the study for assessment. The assessments will be scheduled as screening (week −2 to 0), baseline (week 0), and interim (at the end of week 6) and the final (at the end of week12). The flow chart of the trial is shown in Figure 1.

**Figure 1 F1:**
[figure not shown]
Flow diagram of the trial.

### Ethics approval and consent of the participants

2.2

The trial protocol (NM_HT083, version 1.0, date October 14, 2019) was approved by the ethics committee of the Uijeongbu St. Mary's Hospital, The Catholic University of Korea [UC19HDSE0143]. The participants will be informed about the study purpose, procedure, inclusion and exclusion criteria, test product, and the possible side effects. A written consent will be obtained from all the participants and each participant will be given the signed consent form by the investigator. All the details of the study and the personal information of the participants will be kept confidential and only be accessible to the authorized investigators. The final trial dataset will be accessible to the principal investigator and the sponsor. The trial protocol and the dataset can be accessed from the corresponding author upon a legitimate request. After completion, the results of the trial will be published in a peer-reviewed journal. The investigators have no financial or any other interests in regards to the trial.

### Participants

2.3

#### Inclusion criteria

2.3.1

Subjects who meet all the below criteria will be qualified and enrolled in the study:

Male or female adults aged between 35 and 70 years of age.Subjects with a visual analog scale (VAS) score of more than 30 mmSubjects with Kellgren and Lawrence grade I or II determined by X-raySubjects who agree to participate in the clinical trial voluntarily and sign the informed consent form.

#### Exclusion criteria

2.3.2

Subjects who have one or more of the following characteristics will not be considered for the study.

A person who has arthritis other than OA.Those who have clinically significant cardiovascular, autoimmune, infectious or neoplastic diseases in addition to joint pain.Hypertension patients not controlled by drugs with more than 160 mmHg systolic blood pressure or more than 100 mmHg diastolic blood pressure.Diabetic patients whose fasting blood glucose level is above 180 mg/dl).A person who has aspertate aminotransferase (GOT) or alanin aminotransferase (GPT) level 3 times higher than the normal upper limit.Abnormal creatinine level (more than twice the normal upper limit).Those who have taken arthritis medicines or dietary supplements for joint health within 2 weeks of visit.Subjects who have taken physical or herbal therapies (acupuncture, depression, moxibustion, etc.) for degenerative bone disease within 2 weeks of visit.Subjects who participate in other intervention trials within two months of visit 1 or plan to participate in other intervention trials after the commencement of this study.Women who are pregnant, lactating, or planning to become pregnant within 3 months.A person with mental illness or drug addiction or who is under anti-depression treatment.A person who is sensitive or allergic to food ingredients.A person who has trouble or difficulties participating in the trial as judged by the investigator.

#### Withdrawal and dropout

2.3.3

According to the Declaration of Helsinki, any participant has the right to leave the trial at any time without giving a reason. Participants might be withdrawn from the study to ensure their safety by the investigator. Investigators also possess the right to withdraw a participant from the study for any of the following reasons:

A significant violation of the protocol.In case of a serious adverse event.Subject's refusal to continue with the trial.Subject withdraws the consent.When a subject is unable to ingest the test product or the placebo.Receiving any medication or treatment which may interfere or influence the test result.For any safety reasons.Pregnancy.

### Recruitment

2.4

The participants will be recruited under Uijeongbu St. Mary's Hospital, The Catholic University of Korea, South Korea. The recruitment for the clinical trial will be advertised through posters in public places like hospitals and subways after the approval from the institutional review board. The posters will contain information on the aim and the procedure of the trial including the sponsor, the hospital, selection criteria, and the product details.

### Randomization and blinding

2.5

A randomization list will be created by an independent analyst using block randomization method in SAS version 9.2 (USA). Participants will be given a randomized code and will receive the treatment product labeled with the same code. Participants will be randomly allocated to either the test or the placebo group in a 1:1 ratio. The placebo will be used to compare the efficacy of the test product. All participants and the research personnel will remain blinded to the assigned treatment until the end of the trial. The appearance of the test food and the placebo product will be identical. Unblinding will be permissible under emergency circumstances which are defined in the study protocol.

### Intervention

2.6

The test product is a 500 mg white tablet containing HT083, crystalline cellulose, silicon dioxide, magnesium stearate, hydroxypropylmethylcellulose, glycerine fatty acid ester, and titanium dioxide. A 500 mg placebo product contains crystalline cellulose, maltodextrin, silicon dioxide, magnesium stearate, hydroxypropylmethylcellulose, fatty acid ester, and titanium dioxide. Participants will be instructed to take 2 tablets a day, 1 in the morning and 1 at night in order to have a dose of 1 g per day for 12 weeks. The unused tablets should be required to be returned to the test center for evaluating the subjects’ adherence to the trial. The test and placebo products have been manufactured by NeoNutra Co. Ltd (Seoul, Korea) in a GMP-certified facility. The trial schedule is presented in Table 1.

**Table 1 T1:**
[figure not shown]
Trial Schedule.

### Prohibited concomitant drugs and therapies

2.7

The use of the following drugs and therapies may interfere with the evaluation of safety, efficacy, and tolerability of the test product. Therefore, the drugs and therapies listed below will be restricted during the intervention period:

Acetaminophen.Aspirin and anti-inflammatory drugs.Medication for degenerative arthritis.Hyaluronic acid and corticosteroids.Korean traditional medicines to treat OA.Dietary supplements for joint health.Physiotherapy or herbal treatments for degenerative arthritis (acupuncture, cupping therapies, moxibustion).

All Information about concomitant drugs and therapies will be recorded in the case report form.

### Outcome evaluation

2.8

The following outcomes will be evaluated by trained evaluators during each visit.

#### Primary outcomes

2.8.1

Korean-Western Ontario and McMaster Universities (K-WOMAC) index. The K-WOMAC index will measure changes in joint pain at the end of week 6 and 12 to compare those with the baseline scores.

#### Secondary outcomes

2.8.2

Visual analog scale (VAS), which evaluates joint pain as compared with the baseline score.Korean-Short Form Health Survey 36 (KSF-36). The KSF-36 index will assess the physical and mental states of the subjects at the end of week 6 and 12.Subject's self-assessment on the change of physical and mental conditions.Investigator's evaluation based on subject's physical activity, symptoms, and emotional state.Erythrocyte sedimentation rate (ESR) and C-reactive protein (CRP) levels to measure the inflammatory markers after 12 weeks of study.

#### Safety outcomes

2.8.3

The safety outcome variables are adverse event, vital signs (blood pressure, pulse rate, body weight etc.), clinical test results, and echocardiogram result.

### Data management and quality control

2.9

All data gathered throughout the study will be recorded in the case report form in a timely manner and will be open for the monitor to review the status of the participants. The Clinical Research Associate from the sponsor will regularly monitor and review the data with the investigator for any missing or spurious data. All the resolutions regarding the data will be recorded in the database. Clean dataset will be provided to the analysts. A data monitoring committee (DMC) will not be needed as the test product is low-risk and there will be no interim analysis. Auditing will not be conducted for this trial.

### Sample size

2.10

The sample size will be calculated following a previously described method where the VAS score in the test group decreased from ∼4.2 to ∼25.4, whereas the VAS score in the placebo group increased from ∼40.9 to ∼41.^[6]^ We also assume that the change in the VAS score in our test and placebo groups will be −16.6 and +0.1, respectively. The following parameters will be considered to determine the size of the sample:

Superiority test

Level of significance, a = 0.05 Two-sided test

b = 0.2, power of test = 80%

Ratio of the number of subjects in the test and placebo groups, l = 1, n_t_ (subject number of the test group) = ln_c_ (subject number of the placebo group)

Difference between the groups, D = 16.7

Standard deviation, s = 27.04 (in both groups)

We assume that with a dropout rate of 25%, 37 participants will be included in each group.

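### The 80% power is calculated for VAS, a secondary outcome; the primary outcome, K-WOMAC, has no planning difference or SD, so its power cannot be determined

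*Protocol article*

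**What the plan says.** Section 2.8.1 (Primary outcomes) lists one measure, the "Korean-Western Ontario and McMaster Universities (K-WOMAC) index", and adds: "The K-WOMAC index will measure changes in joint pain at the end of week 6 and 12", compared with baseline.

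Section 2.8.2 (Secondary outcomes) opens with "Visual analog scale (VAS), which evaluates joint pain as compared with the baseline score".

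Section 2.10 (Sample size) is the only place where the trial's size is justified. It takes VAS scores from an earlier trial and continues: "We also assume that the change in the VAS score in our test and placebo groups will be" −16.6 and +0.1. The remaining inputs are "Difference between the groups, D = 16.7", an SD of 27.04 in both groups, equal allocation, "Level of significance, a = 0.05 Two-sided test" and "b = 0.2, power of test = 80"%. It ends with 37 participants per group and a 25% dropout rate.

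Section 2.11 (Statistical analysis) analyses K-WOMAC first, and VAS separately with the other secondary measures. For K-WOMAC, the between-group comparison is a t test or a Wilcoxon rank sum test.

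The Methods paragraph of the abstract gives a total of 100 participants and then says: "Treatment results will be assessed using a visual analog scale (VAS), Korean-Short Form health survey-36 score (SF-36), personal evaluation, and laboratory analysis". K-WOMAC is not in that list.

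**The concern.** A power statement tells the reader how likely the primary test is to detect an effect worth planning for. Here the statement and the primary test concern different instruments. Power depends on the standardised difference, which in turn depends on how far each scale moves and how much it varies. The VAS value cannot be carried over to K-WOMAC without an argument, and the article offers none.

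Two things are at stake. First, a reader will take 80% as the power of the trial, when nothing supports that for the outcome on which the trial is to be judged. Second, a K-WOMAC result that is not significant could not be set against any planned effect, although its confidence interval would still be informative. The abstract adds to the difficulty: someone who reads only the abstract and section 2.10 would not learn from either that K-WOMAC is the primary outcome.

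**Working it through.** **Step 1: which outcome each input belongs to.**

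| Item | Value | Outcome | Section |
|---|---|---|---|
| Primary outcome | K-WOMAC | K-WOMAC | 2.8.1 |
| Assumed changes | −16.6 (test), +0.1 (placebo) | VAS | 2.10 |
| Difference D | 0.1 − (−16.6) = 16.7 | VAS | 2.10 |
| SD | 27.04, given with these changes | VAS | 2.10 |
| Alpha, power | two-sided 0.05, 80% | attached to the VAS inputs | 2.10 |
| K-WOMAC difference or SD | not given | – | – |

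**Step 2: the plan's own figure, for VAS.** The standardised difference is 16.7/27.04 = 0.618. The usual formula for two means gives

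n per group = 2 × (1.960 + 0.842)² / 0.618² ≈ 41.2, so 42 evaluable per group.

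With the exact t calculation, 42 gives 79.9% and 43 gives 80.8%, so 43 are needed. Allowing for 25% dropout, 42/0.75 = 56 per group (42 × 1.25 = 52.5, so 53, by the cruder inflation). A one-sided test would need 33, or 33/0.75 = 44 with dropout. None of these is 37.

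**Step 3: what 37 could mean.**

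- Evaluable: 50 × 0.75 = 37.5, which fits the total of 100 in the abstract.
- Enrolled: 37 × 0.75 = 27.75, about 28 evaluable. The total would then be 74, which does not fit 100.

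Section 2.10 does not say which is meant. Exact t power for the VAS inputs is:

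| Evaluable per group | VAS power at 0.618 SD |
|---|---|
| 28 | 62% |
| 37 | 75% (74.6%) |
| 50 | 86% |

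**Step 4: what can be said about K-WOMAC.** Without a K-WOMAC difference and SD there is no power to compute. What does follow is the standardised difference d detectable with 80% power. It solves power(n, d) = 0.80 for a two-sample t test at two-sided 0.05, with 2n − 2 degrees of freedom and noncentrality d × √(n/2). The normal approximation d = 2.802 × √(2/n) is shown as a check.

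| Evaluable per group | Detectable d, exact t | Normal approximation |
|---|---|---|
| 28 | 0.76 | 0.75 |
| 37 | 0.66 | 0.65 |
| 50 | 0.57 | 0.56 |

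**Step 5: illustration only.** The K-WOMAC effects below are assumed; the document gives none. They are placed on both sides of the VAS value. With 37 evaluable per group, exact t power is:

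| Assumed K-WOMAC d | 0.3 | 0.4 | 0.5 | 0.6 | 0.7 | 0.8 |
|---|---|---|---|---|---|---|
| Power | 25% | 40% | 56% | 72% | 84% | 92% |

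The spread shows how much depends on a quantity that the plan does not state.

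**The case against.** The best defence is that VAS is a reasonable stand-in. Sections 2.8.1 and 2.8.2 describe both instruments as measuring joint pain, VAS is the pain entry criterion in section 2.3.1, and planning from a related measure is common when data on the primary outcome are lacking. The full protocol, which is not shown, may give that reason. This has some weight, but it does not rescue the power statement. The article prints a complete set of inputs and a power figure, does not say that they concern a secondary outcome, and does not argue that 0.62 SD carries over to K-WOMAC.

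Two stronger readings are tempting, and the document supports neither.

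- *That the trial is underpowered on K-WOMAC.* A reader might infer this from power of 25% to 72% at 0.3 to 0.6 SD. Those effects are assumed and lie below the only effect in the document, 0.62 SD. Nothing says that K-WOMAC responds less than VAS, and at 0.7 or 0.8 SD the power at 37 per group exceeds 80%. The power is unknown; it has not been shown to be low.
- *That the document names two rival primary outcomes.* It does not. Section 2.8 assigns the roles explicitly, section 2.11 takes K-WOMAC first, and the abstract designates no primary outcome at all. Its fault is an omission.

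One might also propose to remove the mismatch by making VAS primary. That would not make the 80% true, since 37 evaluable per group give 74.6% for VAS and 43 are needed. It would also change the primary outcome of a registered, ethics-approved trial to suit a calculation.

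**Conclusion.** The point holds as a mismatch of endpoints. The only sample-size calculation and its 80% power concern change in VAS, a secondary outcome. The primary comparison on K-WOMAC has no planning difference or SD, and its power cannot be determined from the document.

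The size of the problem is best given as the detectable effect: 0.76, 0.66 or 0.57 SD with about 28, 37 or 50 evaluable per group. These figures assume a two-sample t test at two-sided 0.05 with equal groups. The range is wide because section 2.10 leaves the meaning of 37 open. Separately, 80% is not reached for VAS either if 37 are evaluable; the stated inputs then give about 75%.

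The statement is wrong as written and should be corrected, because it concerns the test on which the trial is to be judged.

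**What to change.** Before unblinding:

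1. Keep K-WOMAC as the primary outcome. Do not switch to VAS.
2. In section 2.10, say that the VAS calculation concerns a secondary outcome.
3. State whether 37 per group means enrolled or evaluable, and reconcile it with the total of 100 in the abstract.
4. Replace the 80% claim for the trial with the standardised K-WOMAC difference detectable with 80% power at the resulting number: 0.76 SD for about 28 evaluable per group, 0.66 SD for 37, or 0.57 SD for 50. If the VAS calculation is kept, correct its power too (about 75% with 37 evaluable).
5. Name K-WOMAC as the primary outcome in the abstract.

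The cost is a change of wording and a less favourable stated figure. No patients are added, and the primary outcome and its analysis stay as they are.

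### The sample-size inputs in section 2.10 need 42 to 43 evaluable participants per group for 80% power; the stated 37 per group gives about 75%.

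*Protocol article*

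**What the plan says.** All inputs stand in section 2.10 (Sample size) of the protocol article.

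- Test: "Superiority test"; "Level of significance, a = 0.05 Two-sided test"; beta 0.2, so 80% power.
- Effect: the plan assumes that "the change in the VAS score in our test and placebo groups will be −16.6 and +0.1, respectively", hence "Difference between the groups, D = 16.7".
- Variability: a standard deviation of 27.04, the same in both groups.
- Allocation: "Ratio of the number of subjects in the test and placebo groups, l = 1".
- Result: "We assume that with a dropout rate of 25%, 37 participants will be included in each group".

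The Methods paragraph of the abstract gives a total of 100 participants, randomised 1:1. Section 2.10 does not mention 100, and it does not say whether 37 is counted before or after dropout.

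**The concern.** The section gives every input that a two-group comparison of means requires, so its result can be checked directly. A standardised difference of 16.7/27.04 = 0.62 at two-sided 5% and 80% power should need just over 40 per group, so 37 is too few. The section also plans for 25% dropout, which should push the number enrolled well above the number evaluable.

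The stated power is at stake. The planned enrolment of 100 appears to be built on 37, and anyone reading a null result would take the risk of a missed effect to be 20%. If the inputs are right, that risk is larger.

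**Working it through.** **Inputs** (section 2.10): D = 16.7; s = 27.04; two-sided alpha 0.05 (z = 1.960); power 80% (z = 0.842); 1:1 allocation; dropout 25%. From the abstract: 100 enrolled, so 50 per group.

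**1. Required number per group**

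n = 2 (z_alpha + z_beta)² (s/D)²

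- (s/D)² = (27.04/16.7)² = 2.622
- (1.960 + 0.842)² = 7.849
- n = 2 × 7.849 × 2.622 = 41.15, so **42**

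The two-sample t test (noncentral t) gives 42.14, so **43**; its power at 42 is 79.9%. The plan's 37 is not reproduced.

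**2. Attempts to arrive at 37**

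| Variant | Per group |
|---|---|
| Two-sided 5%, 80% power | 42 |
| The same, inflated for dropout: n/0.75, or n × 1.25 | 56, or 53 |
| One-sided 5%, 80% power | 33 (32.4 before rounding) |
| The same, inflated for dropout: n/0.75, or n × 1.25 | 44, or 42 |
| Two-sided 5%, **75%** power: 2 (1.960 + 0.674)² × 2.622 = 36.4 | 37 |

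At 80% power, 37 would also follow from a standard deviation of about 25.6 or a difference of about 17.6. The article states none of these, so the origin of 37 stays open.

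**3. Power with 37 evaluable per group**

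- Standard error = 27.04 × √(2/37) = 6.287
- 16.7/6.287 = 2.656
- Power = Φ(2.656 − 1.960) = Φ(0.696) = **75.7%**; noncentral t **74.6%**
- Difference detectable with 80% power = (1.960 + 0.842) × 6.287 = **17.6 mm**; t test **17.9 mm**

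**4. What 37 counts**

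- *Evaluable:* 37/0.75 = 49.3, so 50 per group and 100 in total, which agrees with the abstract. Power is as in step 3.
- *Enrolled:* 37 × 0.75 = 27.75, about 28 evaluable. Power is 62% (t test) or 64% (normal). The total would be 74, which disagrees with the abstract.

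**5. Enrolment needed for 80% power with 25% dropout**

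- 42/0.75 = 56 per group, 112 in total
- 43/0.75 = 57.3, so 58 per group, 116 in total

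**6. A figure beside the calculation**

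The section describes a fall in the earlier test group's VAS, but prints a start of about 4.2 and an end of about 25.4, which is a rise of 21.2. A start of 42.0 would give 42.0 − 25.4 = 16.6, the change that the plan assumes. Because D is stated outright, this does not affect steps 1 to 5.

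**The case against.** The arithmetic is not in dispute, but its weight can be.

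- **The shortfall is modest and conditional.** Power is about 75% only if the full 25% drop out. With all 50 per group evaluable it would be 86 to 87%, and it reaches 80% if 42 or 43 of 50 are retained, that is, with dropout of no more than 14 to 16%. This is true and worth knowing. But 25% is the protocol's own assumption, and the power claim has to hold under it.
- **Nothing else in the trial is harmed.** The error causes no bias and no inflation of type I error, and no more participants are required. That makes the correction cheap, but the stated power is still wrong.
- **The calculation concerns VAS, a secondary outcome.** Section 2.8.1 names K-WOMAC as primary. This stands as a separate matter: correcting the VAS power leaves the article with no power statement for its primary outcome.
- **Reading 37 as evaluable is an inference.** This also stands. The sentence can be read as enrolment, and the sponsor should confirm which is meant. The other reading makes the shortfall larger.
- **The 4.2 figure is probably a slip of the decimal point.** Agreed. The cited source is not at hand, so only the inconsistency within the section can be shown, and the conclusion does not rest on it.

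**Conclusion.** The concern holds. The published inputs and the published result in section 2.10 contradict each other, and an unseen analysis plan cannot make both true. On the reading kindest to the plan, the group size is 5 to 6 short and power is about 75% instead of 80%. On the other reading it is about 62%. The main figure assumes that 37 is the evaluable number, that D = 16.7 and s = 27.04 are the intended inputs, and that the planned test is the two-group comparison of mean VAS change described there.

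**What to change.** Keep the planned 100 and correct the statement in section 2.10. Once the sponsor has confirmed that 37 is the evaluable number, the text could read:

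> Fifty participants per group will be randomised. With 25% dropout, 37 per group will be evaluable, which gives about 75% power for a VAS difference of 16.7 mm (standard deviation 27.04, two-sided 5%); 80% power applies to a difference of 17.9 mm.

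In the same edit, check the printed starting value of about 4.2 against the cited source, and correct it to the value that yields −16.6.

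The cost is a wording change and a slightly less favourable power figure, with no extra enrolment. If the sponsor prefers to keep the 80% claim with these inputs and 25% dropout, enrolment must rise from 100 to 112 (normal formula) or 116 (t test).

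### Section 2.10 most likely labels the evaluable number (37 per group) as the number included, which does not match the abstract's 100; and 37 evaluable per group gives about 75% power for VAS change, not the stated 80%

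*Protocol article*

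**What the plan says.** Section 2.10 (Sample size) sets the design as a "Superiority test" with "Level of significance, a = 0.05 Two-sided test" and "b = 0.2, power of test = 80"%, at equal group sizes. It assumes that "the change in the VAS score in our test and placebo groups will be −16.6 and +0.1, respectively", and hence "Difference between the groups, D = 16.7", with "Standard deviation, s = 27.04 (in both groups"). It closes with the statement that "with a dropout rate of 25%, 37 participants will be included in each group". It gives no total.

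The abstract (Methods) says "A total of 100 eligible participants will be divided into two groups" at 1:1, which is 50 per group. Section 2.5 (Randomization and blinding) confirms the 1:1 ratio but gives no number.

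No sentence says whether 37 is counted before or after dropout, and none connects 37 with 100. VAS, on which the calculation is based, is listed under secondary outcomes (2.8.2). The primary outcome is K-WOMAC (2.8.1).

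**The concern.** Two numbers in one article appear to answer the question of how many people enter the trial: 74 (2 × 37) from section 2.10 and 100 from the abstract, a gap of 26. Because 2.10 names the dropout rate in the same sentence as the 37, the natural reading is that dropout has already been added. Anyone judging later whether recruitment was completed or stopped early would have two numbers to judge it against.

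The second issue is whether 37, under either meaning, delivers the power that the section claims. If it does not, making the two numbers agree would leave a consistent but still wrong sample size statement.

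**Working it through.** **Inputs**, all from section 2.10 unless noted: difference D = 16.7 (from −16.6 and +0.1); SD s = 27.04 in both groups; two-sided α = 0.05 (z = 1.960); power 80% (z = 0.842); equal groups; dropout 25%; 37 per group. The total of 100 is from the abstract.

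**Step 1. Try to reproduce 37 from the inputs.**

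n per group = 2 × [s × (1.960 + 0.842) / D]² = 2 × (27.04 × 2.802 / 16.7)² = 41.15, so 42 (normal approximation).

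The two-sample t calculation gives 42.14, so 43.

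| Variant | Before dropout | After dropout, n/(1 − 0.25) | After dropout, n × 1.25 |
|---|---|---|---|
| Two-sided, normal | 42 | 56 | 53 |
| Two-sided, t | 43 | 58 | 54 |
| One-sided, normal | 33 | 44 | 42 |

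None of these returns 37, either as an evaluable or as an enrolled number. For 37 per group to give 80% power (normal approximation), D would have to be about 17.6 at the stated SD, or the SD about 25.6 at the stated D.

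**Step 2. Link 37 to 100.**

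- As an evaluable number: 37 / 0.75 = 49.3, rounded up to 50 per group, 100 in total. This matches the abstract. In reverse, 50 × 0.75 = 37.5.
- With the other inflation convention: 37 × 1.25 = 46.25, so 47 per group, 94 in total. This does not match.
- As an enrolled number: 2 × 37 = 74. This does not match.

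**Step 3. Power under each reading**, for VAS change. Normal approximation: power = Φ[D / (s × √(2/n)) − 1.960].

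- n = 37: s × √(2/37) = 6.287; 16.7 / 6.287 = 2.656; Φ(0.696) = 75.7%.
- n = 28: s × √(2/28) = 7.227; 16.7 / 7.227 = 2.311; Φ(0.351) = 63.7%.

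| Randomised in total | Evaluable per group after 25% dropout | Power, normal | Power, t |
|---|---|---|---|
| 74 | 27.75, about 28 | 63.7% | 62.2% |
| 100 | 37.5, taken as 37 | 75.7% | 74.6% |
| 112 (56 per group) | 42 | 80.8% | 79.9% |
| 116 (58 per group) | 43.5, taken as 43 | 81.7% | 80.8% |

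Using 27.75 unrounded in the first row gives 63.3% and 61.8%.

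**The case against.** The best defence is that there is only one enrolment target. The article states one total, 100, and nowhere states 74. The 25% in the same sentence of 2.10 takes 37 to the abstract's 50 per group once rounded up. On that view the fault is one badly chosen verb. This largely stands, and it is why the point is framed as a mislabelled number.

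A reader might infer that the trial has two rival targets and will run at about 62% power. The documents do not support that. The 62% arises only if recruitment stops at 74, which is the less coherent reading. Nor do they show that the randomisation list was sized from 37: section 2.5 gives no list length and does not refer to 2.10.

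It can also be said that the article condenses a fuller protocol, and that the flow diagram, not available for this review, may carry the operational number. That would excuse an omission. Here both figures are printed in the article and do not agree as worded.

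The defence does not reach the power statement. If 37 is the evaluable number, as the defence requires, the section's own inputs give about 75%.

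**Conclusion.** Section 2.10 is wrong as written in two respects.

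First, its 37 per group described as included does not fit the abstract's 100. The likeliest explanation is that 37 is the expected evaluable number. That is an inference from 37/0.75 rounding up to 50, not something the article states, and it is weakened a little because 37 cannot be derived from the inputs as an evaluable number either.

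Second, the stated 80% power does not follow. With 100 randomised and 37 evaluable per group, power is about 75% (74.6% by t, 75.7% by normal approximation). The stated 80% needs 42 to 43 evaluable and 56 to 58 randomised per group, 112 to 116 in total. Taken literally, 74 randomised would leave about 28 per group and about 62% power (t).

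These figures assume exactly 25% dropout in each group, an analysis of evaluable participants only, and the section's own D and SD. They are for VAS change. A reader might take them as the power of the trial's main comparison, but the primary outcome is K-WOMAC and the article gives no difference or SD for it, so no power for the primary outcome can be derived here.

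**What to change.** Replace the closing sentence of section 2.10 with wording such as: 100 participants (50 per group) will be randomised; with 25% dropout about 37 per group are expected to be evaluable, giving about 75% power for a difference of 16.7 in VAS change (SD 27.04, two-sided 0.05). Replace the 80% power and the matching β in the parameter list so that they agree, use 100 wherever a total is given, and add that this power is for VAS, a secondary outcome, and not for the primary K-WOMAC.

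The cost is a few lines of text and a slightly less favourable power figure. The announced total of 100 does not change. If the sponsor would rather keep 80%, the total has to rise to 112 to 116, that is, 12 to 16 more participants. Relabelling 37 alone is not enough, because it would leave the 80% uncorrected.
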